## Abstract

**Background:**

Prostate cancer is the most common cancer in males in the UK and affects around 105 men for every 100,000. The role of radiotherapy in the management of prostate cancer significantly changed over the last few decades with developments in brachytherapy, external beam radiotherapy (EBRT), intensity-modulated radiotherapy (IMRT), and image-guided radiotherapy (IGRT). One of the challenging factors of radiotherapy treatment of localized prostate cancer is the development of acute and late genitourinary and gastrointestinal toxicities.
The recent European guidelines suggest that there is no consensus regarding the timing of high-dose rate (HDR) brachytherapy and EBRT. The schedules vary in different institutions where an HDR boost can be given either before or after EBRT. Few centers deliver HDR in between the fractions of EBRT.

**Objective:**

Assessment of acute genitourinary and gastrointestinal toxicities at various time points to better understand if the order in which treatment modality is delivered (ie, HDR brachytherapy or EBRT first) has an effect on the toxicity profile.

**Methods:**

Timing of HDR brachytherapy with EBRT in Prostate CAncer (THEPCA) is a single-center, open, randomized controlled feasibility trial in patients with intermediate and high-risk localized prostate cancer. 
A group of 50 patients aged 18 years old and over with histological diagnosis of prostate cancer (stages T1b-T3BNOMO), will be randomized to one of two treatment arms (ratio 1:1), following explanation of the study and informed consent. Patients in both arms of the study will be treated with HDR brachytherapy and EBRT, however, the order in which they receive the treatments will vary. In Arm A, patients will receive HDR brachytherapy before EBRT. In Arm B (control arm), patients will receive EBRT before HDR brachytherapy. 
Study outcomes will look at prospective assessment of genitourinary and gastrointestinal toxicities. The primary endpoint will be grade 3 genitourinary toxicity and the secondary endpoints will be all other grades of genitourinary toxicities (grades 1 and 2), gastrointestinal toxicities (grades 1 to 4), prostate-specific antigen (PSA) recurrence-free survival, overall survival, and quality of life.

**Results:**

Results from this feasibility trial will be available in mid-2016.

**Conclusions:**

If the results from this feasibility trial show evidence that the sequence of treatment modality does affect the patients’ toxicity profiles, then funding would be sought to conduct a large, multicenter, randomized controlled trial.

**Trial Registration:**

International Standard Randomized Controlled Trial Number (ISRCTN): 15835424; http://www.isrctn.com/ISRCTN15835424 (Archived by WebCite at http://www.webcitation.org/6Xz7jfg1u).

## Introduction

### Disease Background

Prostate cancer is the most common cancer in males in the UK, affecting around 105 men for every 100,000 [1]. The role of radiotherapy (RT) in the management of prostate cancer significantly changed over the last few decades with developments in brachytherapy (BT), external beam radiotherapy (EBRT), intensity-modulated radiotherapy (IMRT), and image-guided radiotherapy (IGRT). One of the challenging factors of radiotherapy treatment of localized prostate cancer is the development of acute and late genitourinary and gastrointestinal toxicities. There are several studies and case series published in the literature assessing the toxicities developed during EBRT and brachytherapy treatment for prostate cancer.

### Background for Study

EBRT and brachytherapy emerged as the mainstays of localized prostate cancer treatment in recent years. Brachytherapy can be delivered either in low-dose rate (LDR) or in high-dose rate (HDR). The low-risk, localized prostate cancers can be treated with low-dose brachytherapy or by prostatectomy, whereas the intermediate and high-risk localized prostate cancers are usually treated with EBRT alone or in combination with HDR brachytherapy (HDR-BT). HDR monotherapy in this patient group is not routinely practiced unless as part of a study. Radiation dose escalation has been proven to be effective in biochemical response and clinical outcomes in prostate cancer. However, increased toxicity limits the total dose of radiation that can be safely administered [2-4]. Combining external beam radiotherapy with a brachytherapy boost has been effective in tumor control, allowing for significant dose escalation without any change in acute and late toxicities in comparison to external beam radiotherapy alone [5].

The relative sensitivity of radiotherapy depends on the alpha/beta ratio. This ratio expresses the sensitivity to radiation fraction size and estimates the impact of the given radiation schedule on tumor control and toxicity. There is increasing evidence to support the alpha/beta ratio for prostate cancer to be as low as 1.5 Gy. The evidence indicates that a hypofractionated radiation schedule—larger dose per fraction with smaller number of fractions—would offer optimal tumor control [6-9]. As a result, the practice of combining EBRT with HDR brachytherapy is gaining momentum in clinical practice. However, the current practice across the globe differs in both radiation doses and in the timing of each modality delivered.

The recent European guidelines suggest that there is no consensus regarding the timing of HDR brachytherapy and EBRT. The schedules vary in different institutions where an HDR boost can be given either before or after EBRT. Few centers deliver HDR in between the fractions of EBRT [10].

The EBRT doses range from 37.5 Gy in 13 fractions (2.88 Gy per fraction) to 45 Gy in 25 fractions (1.8 Gy per fraction) when given with HDR. The total HDR brachytherapy dose can be delivered in fractions, however a single dose of 15 Gy is gaining acceptance across the world due to its logistical advantage [10]. The time gap between the two radiotherapy modes of delivery is generally within 21 days.

The toxicity profile of radiation therapy is dependent on the type of modality used to deliver the treatment, and whether the treatment is delivered as a combined modality or standalone treatment [11]. A randomized phase III trial where EBRT was delivered before HDR showed that the 5- and 7-year incidence for patients with any severe urinary symptom was 26% and 31%, respectively, for those treated with EBRT and HDR-BT delivered sequentially. For patients given EBRT alone, the 5- and 7-year incidence was 26% and 30%, respectively (log rank *P*=.5). The incidence of severe bowel events for the EBRT/HDR combination group was considerably lower—7% and 6% at 5 and 7 years, respectively (log rank *P*=.8) [5]. On the other hand, a single-arm phase II study was performed to determine the toxicity profile of EBRT delivering a dose of 37.5 Gy in 15 fractions that was given after a single-fraction HDR boost of 15 Gy. In this study, Morton et al found acute grade 2 and grade 3 genitourinary toxicity in 62% and 1.6% of patients, respectively, and acute grade 2 gastrointestinal toxicity in 6.5% of patients, with no grade 3 gastrointestinal toxicity [12].

Both acute and late toxicity assessments in prostate cancer patients are assessed by various tools. For example, the European Organisation for Research and Treatment of Cancer Quality of Life Questionnaire for Cancer Patients (EORTC QLQ-C30), the European Organisation for Research and Treatment of Cancer Quality of Life Questionnaire for Prostate Cancer Patients (QLQ PR25), the National Cancer Institute Common Terminology Criteria for Adverse Events (CTCAE) grading system, the Functional Assessment of Cancer Therapy-Prostate (FACT-P), version 4, the International Prostate Symptom Score (IPSS), the International Index of Erectile Function Scale (IIEFS), and the Expanded Prostate Cancer Index Composite (EPIC) questionnaire may be used for toxicity assessments. Furthermore, the same data collection tools are used to measure health-related quality of life.

### Rationale and Risks/Benefits

There is no consensus about the timing of HDR brachytherapy when treating prostate cancer along with EBRT. The advantages of using HDR brachytherapy before EBRT are that patients could potentially be identified who are not suitable for brachytherapy early in the treatment process. As the patients would be radiotherapy naïve, there would be less chance of soft tissue injury during the brachytherapy process if BT is given first. However, having brachytherapy first can be logistically difficult in a busy radiotherapy unit in terms of planning and arranging delivery of EBRT within 2 to 3 weeks of BT. Moreover, if the patients develop acute urinary complications during brachytherapy they would need to continue with EBRT with a urinary catheter, which could potentially prolong the duration of the catheter in situ and cause significant patient discomfort.

On the other hand, delivering EBRT first is logistically easier to arrange and could theoretically make the hypofractionated radiation dose of brachytherapy more effective, as tumor cells could become more radiosensitive due to molecular changes having been induced by EBRT. However, normal tissue damage due to delivery of EBRT first could make the brachytherapy procedure difficult with increased risk of toxicity. It is, therefore, essential to know whether there are any significant differences in toxicities and treatment outcomes, especially acute urinary toxicity among the two treatment approaches.

This randomized feasibility study will look at the treatment arms according to the timing of HDR brachytherapy—either before or after EBRT—and their toxicity profiles. The study is called Timing of HDR brachytherapy with EBRT in Prostate CAncer (THEPCA). Assessment of acute and late toxicities and other parameters in these two arms at various time points will enable appropriate sequencing of EBRT and HDR therapy resulting in an optimal level of reduced toxicity. The treatments from both arms will be delivered with standard planning techniques. The incidence of grade 3 genitourinary toxicity is 1.6% in this cohort of patients [5]. Additionally, this feasibility study will also explore the challenges of image-guided radiotherapy planning between the two study arms. Provided a significant difference between the two treatment arms is achieved following final analysis, consideration will be made to use this to inform the development of a further pivotal study to look more deeply into the toxicity and other parameters related to the treatment.

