#### Primary and Secondary Endpoints

The primary endpoint of this study is the presence of grade 3 genitourinary toxicity in patients. The secondary endpoints of this study are the presence of all other grades of genitourinary toxicity (ie, grades 1 and 2), the presence of gastrointestinal toxicity (ie, grades 1 to 4), prostate-specific antigen (PSA) recurrence-free survival, overall survival, and quality of life (QoL).

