### Statistical Considerations

#### Primary Endpoint Analysis

Percentages will be compared using Fisher’s exact test. This analysis will be carried out after the end of the follow-up at 12 months.

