#### Sample Size

In this feasibility study, the sample size has not been determined according to statistical principles, but is the number judged to be suitable for evaluating the suitability of the processes and procedures of running the study, and for assessing the patient experience and adherence in the study. To this end, two samples of 25 patients—50 overall—will be randomized to the two treatments.

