## Discussion

If the results from this feasibility trial show evidence that the sequence of treatment modality does affect the patients’ toxicity profiles, then funding would be sought to conduct a large, multicenter, randomized controlled trial.

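### Progression to a pivotal trial is tied to a significant between-arm difference, which 25 patients per arm have little chance of showing on the primary endpoint

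*Protocol article*

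**What the plan says.** The condition for going on appears in three places. The Introduction, under Rationale and Risks/Benefits, says: "Provided a significant difference between the two treatment arms is achieved following final analysis, consideration will be made" to using the result to inform a further pivotal study. No endpoint is named. The Discussion, and the Abstract's Conclusions in the same terms, are looser: funding for a large multicentre trial follows "If the results from this feasibility trial show evidence that the sequence of treatment modality does affect the patients’ toxicity profiles".

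The endpoint section states: "The primary endpoint of this study is the presence of grade 3 genitourinary toxicity in patients". For its analysis, the Primary Endpoint Analysis section says: "Percentages will be compared using Fisher’s exact test". The Statistical Analysis section sets all testing at the 5% level.

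The Sample Size section fixes two groups of 25 and says this was not derived statistically. It is "the number judged to be suitable for evaluating the suitability of the processes and procedures of running the study", and for assessing patient experience and adherence.

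On the expected rate, Rationale and Risks/Benefits says: "The incidence of grade 3 genitourinary toxicity is 1.6% in this cohort of patients [5", so the source given is reference 5. Background for Study describes reference 5 as the randomized trial with external beam treatment before brachytherapy. There, the result "acute grade 2 and grade 3 genitourinary toxicity in 62% and 1.6% of patients, respectively" belongs to reference 12, a single-arm study with brachytherapy first.

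**The concern.** A study sized for feasibility is given an efficacy-style condition for what comes next. If the grade 3 event is as rare as the article says, a non-significant result is nearly certain whether or not sequence matters over a wide range of true differences. Read at face value, the condition would let that uninformative result count against the main trial. What 50 patients can show (whether men are recruited, complete both modalities and return complete data) does not appear in the progression statements.

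Because no endpoint is named, the condition also errs in the other direction. Many secondary outcomes are compared at an unadjusted 5%, and any one of them reaching significance by chance could be taken as meeting it.

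The 1.6% is the only rate a reader can use to judge the primary comparison. It carries the wrong reference and lacks the labels that would show how little it says about the control arm.

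**Working it through.** **Inputs.** 25 per arm (Sample Size); Fisher's exact test (Primary Endpoint Analysis); 5% level (Statistical Analysis); 1.6% (Rationale and Risks/Benefits). The article gives no power figure to reproduce. It does not state whether Fisher's test is one- or two-sided; two-sided is assumed.

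**Smallest significant result.** With equal arms and no events in one of them, the two-sided p-value for x against 0 is 2·C(25,x)/C(50,x).

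- 5 v 0: 2 × 53,130 / 2,118,760 = 0.0502, not significant.
- 6 v 0: 2 × 177,100 / 15,890,700 = 0.0223, significant.
- Next boundaries by enumeration: 7 v 1 (p = 0.049) and 9 v 2 (p = 0.037).

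So at least 6/25 = 24% of one arm must have the event.

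**Expected events if both arms are at 1.6%.**

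- Expected number: 50 × 0.016 = 0.8.
- No event: 0.984^50 = 0.446.
- At most one: 0.446 + 50 × 0.016 × 0.984^49 = 0.446 + 0.363 = 0.809.
- Chance of significance: the main term is 6 or more in one arm and 0 in the other, 2 × (2.287 × 10⁻⁶) × 0.984^25 = 2 × (2.287 × 10⁻⁶) × 0.668 = 3.06 × 10⁻⁶. All 26 × 26 tables together give 3.1 × 10⁻⁶.

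**Power with 1.6% in one arm.** This is the sum of the binomial probabilities of all tables with p ≤ 0.05.

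| Rate in other arm | Ratio to 1.6% | Chance of significance |
|---|---|---|
| 3.2% | 2 | 0.008% |
| 5% | 3.1 | 0.09% |
| 10% | 6.25 | 2.5% |
| 15% | 9.4 | 12.7% |
| 20% | 12.5 | 31.8% |
| 24% | 15 | 49.9% |
| 30% | 18.75 | 73.6% |
| 32% | 20 | 79.6% |
| 33% | 20.6 | 82.2% |

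For scale, 80% power for 1.6% v 10% needs about 121 per arm (144 with continuity correction).

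**Sensitivity.** A one-sided 5% test would need 5 v 0 (p = 0.025), since 4 v 0 gives 0.055. With 22 or 23 per arm, 5 v 0 is just significant two-sided (p = 0.048 and 0.049). Neither changes the picture.

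**What the planned interval would show.** For 0/25 in both arms, the Wilson upper limit is z²/(n + z²) = 3.84/28.84 = 13.3%, so the Newcombe 95% interval for the difference is −13.3 to +13.3 percentage points. That shows a reader directly how little the comparison settles.

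**Room for a chance positive.** The two symptom scales (IPSS and IIEFS) are compared at each follow-up. With the four follow-up scores named in the analysis section, that is 2 × 4 = 8 tests. If nothing differs, 8 × 0.05 = 0.4 false positives are expected from these alone, before the lower genitourinary grades and gastrointestinal toxicity.

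**The case against.** The strongest reply is that the condition is not tied to grade 3 genitourinary toxicity. The Introduction names no endpoint and the Discussion speaks of toxicity profiles, so a secondary outcome could satisfy it, and some secondary outcomes have usable power. Grade 2 genitourinary toxicity at 62% v 20% has 83% power, 62% v 30% has 57%, and a 0.8 SD difference in a score has about 81%. This stands, and it rules out describing the condition as an automatic refusal. It does not rescue the condition: the article does not say which result counts, and the comparisons are unadjusted.

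Other stronger readings are tempting and not supported:

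- A reader might infer that significance is impossible whatever the truth. It is not: 6 v 0 is significant, and 1.6% v 30% would be detected 74% of the time.
- A reader might infer that a null result ends the programme. The article speaks of consideration and of seeking funding; it states no binding stop.
- A reader might set the 1.6% (brachytherapy first) against the 26% and 31% (external beam first) in Background for Study and expect a large, detectable gap. Those are 5- and 7-year figures for any severe urinary symptom, against acute grade 3 toxicity, and cannot be compared.
- A reader might say that feasibility is ignored altogether. Radiotherapy planning challenges are a secondary objective and quality of life is an endpoint. Only the progression statements leave out process measures.
- Missing numerical progression thresholds are not a fault of the article; the full protocol may hold them.

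It is also fair to say that the 1.6%, being a brachytherapy-first figure, should not be assumed for both arms. For that reason the table varies the other arm's rate.

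**Conclusion.** The point holds in a limited form and should be fixed. The article conditions the next trial on significance, or evidence of an effect, in a study that it says was not sized statistically. On the primary endpoint the chance of significance is about 3 in a million if both arms are near 1.6%. It stays below 3% for a sixfold difference, and reaches about 80% only when the other arm is at 32–33%, roughly twentyfold. A non-significant primary result would thus be nearly uninformative about sequence. On secondary outcomes the condition can be met, including by chance.

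This rests on a two-sided test, 25 evaluable patients in each arm, and 1.6% applying to at least one arm. That last assumption is weak, because the figure is acute toxicity from one single-arm study with brachytherapy first, and so is not an estimate for the control arm. The reference given for it in Rationale and Risks/Benefits conflicts with Background for Study. This is a separate, minor error, since no sample size depends on it.

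**What to change.** 1. Remove the significance or evidence condition from the Abstract's Conclusions, Rationale and Risks/Benefits, and the Discussion.
2. State that progression rests on the aims in the Sample Size section: processes, patient experience and adherence. The data are already being collected: recruitment from the screening and enrolment logs, the proportion completing both modalities within the protocol's gap, and completeness of the 12-month assessments. Any numerical thresholds can sit in the full protocol.
3. Report the difference in grade 3 genitourinary toxicity, as the endpoint is now defined, as an estimate with the Newcombe 95% interval already planned, and say that it is not a go/no-go test.
4. Change the reference for the 1.6% from 5 to 12, and label it as acute toxicity in a single-arm, brachytherapy-first study that does not estimate the control arm's rate.

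The cost is wording only, with no new patients or data. The pilot gives up a claim to test the sequence effect on its primary endpoint, for which it has little power short of a very large difference.

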### Trial Objectives

#### Primary Objective

The primary objective of this study is the prospective assessment of genitourinary toxicities related to the treatment sequence of HDR brachytherapy and EBRT.

#### Secondary Objectives

The secondary objectives of this study are to assess treatment outcomes, including biochemical response and survival, prospective assessment of gastrointestinal toxicities according to the treatment sequence of HDR brachytherapy and EBRT, and assessment of radiotherapy planning challenges, including image-guided radiotherapy.

#### Primary and Secondary Endpoints

The primary endpoint of this study is the presence of grade 3 genitourinary toxicity in patients. The secondary endpoints of this study are the presence of all other grades of genitourinary toxicity (ie, grades 1 and 2), the presence of gastrointestinal toxicity (ie, grades 1 to 4), prostate-specific antigen (PSA) recurrence-free survival, overall survival, and quality of life (QoL).

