## Methods

### Trial Design

This study will be a randomized, two-arm trial in which intermediate and high-risk prostate cancer patients are treated with both HDR brachytherapy and EBRT. In Arm A, patients will receive HDR brachytherapy before EBRT. In Arm B (control arm), patients will receive EBRT before HDR brachytherapy. The assessment of the acute and late toxicities at various time points will be carried out. The treatment should start within 3 months from the randomization date. This trial has been registered with the International Standard Randomized Controlled Trial Number (ISRCTN) registry (ISRCTN: 15835424).

Toxicity will be assessed using the following tools:

1. International Prostate Symptom Score (IPSS)

2. International Index of Erectile Function Scale (IIEFS)

3. Functional Assessment of Cancer Therapy-Prostate (FACT-P), version 4

4. National Cancer Institute Common Terminology Criteria for Adverse Events (CTCAE), version 4, grading system

The THEPCA study scheme design is shown in Figure 1.

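### Grade 4 genitourinary toxicity belongs to no genitourinary endpoint: the primary endpoint is grade 3 alone and the secondary covers only grades 1 and 2

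*Protocol article*

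**What the plan says.** The section Primary and Secondary Endpoints sets the primary endpoint: "The primary endpoint of this study is the presence of grade 3 genitourinary toxicity in patients". The secondary GU endpoint is "the presence of all other grades of genitourinary toxicity (ie, grades 1 and 2", and next to it the GI endpoint is "the presence of gastrointestinal toxicity (ie, grades 1 to 4". The same list goes on with "prostate-specific antigen (PSA) recurrence-free survival, overall survival, and quality of life (QoL".

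The abstract (Methods) gives the same grades: "The primary endpoint will be grade 3 genitourinary toxicity and the secondary endpoints will be all other grades of genitourinary toxicities (grades 1 and 2". GI toxicity there also runs from 1 to 4.

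Trial Design names the grading scale: "National Cancer Institute Common Terminology Criteria for Adverse Events (CTCAE), version 4, grading system".

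Primary Endpoint Analysis compares percentages with Fisher's exact test after 12 months of follow-up. Safety Endpoints refers back to that analysis and adds no further grade category. Sample Size gives 25 patients per arm and says that the number was not derived statistically. Rationale and Risks/Benefits puts the incidence of grade 3 GU toxicity at 1.6%.

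**The concern.** A severe-toxicity endpoint normally counts everything at or above a threshold. This one counts a single grade. The secondary GU endpoint sounds as if it takes in all remaining grades, but its parenthesis closes the list at grade 2. The GI endpoint in the same sentence shows that the authors had a scale reaching at least grade 4 in mind, so the omission for GU is visible in the text itself. It occurs in both places where the endpoints are listed.

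The primary objective is to assess GU toxicity by treatment sequence. Under the literal definition a grade 4 GU event can leave a patient counted as free of the primary event, while a milder grade 3 event counts against the arm. Any resulting error therefore favours the arm with the more severe event. The Discussion makes evidence that sequence affects toxicity the condition for seeking funds for a large multicentre trial, so the direction of this comparison matters even in a feasibility study.

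**Working it through.** There is no power or sample size figure to reproduce, since the point concerns a definition. The check is which endpoint each GU grade enters, then what one affected patient does to the comparison.

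**Step 1. Where each GU grade counts, as written**

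| GU grade | Primary | Secondary GU | Other endpoint |
|---|---|---|---|
| 1 | no | yes | – |
| 2 | no | yes | – |
| 3 | yes | no | – |
| 4 | no | no | none |
| 5 (fatal) | no | no | overall survival |

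For GI toxicity, grade 4 is named. Nothing in Primary Endpoint Analysis, Safety Endpoints or Statistical Analysis assigns grade 4 GU toxicity to an endpoint.

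**Step 2. Which patients are affected**

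The endpoint is the presence of grade 3. A patient with grade 3 recorded at any time is a primary event, even if grade 4 follows. The patient who is missed has grade 4 or 5 and no recorded grade 3.

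**Step 3. Effect of one such patient**

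Inputs: 25 per arm (Sample Size), all randomized patients analysed (Statistical Analysis).

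- Shift in one arm's percentage: 1/25 = 4 percentage points.
- One such patient in one arm and no other event: 0/25 vs 0/25 as written, 1/25 vs 0/25 as grade 3 or higher.

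**Step 4. Expected number of events**

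Input: 1.6% grade 3 incidence (Rationale and Risks/Benefits).

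- Per arm: 25 × 0.016 = 0.4.
- Whole trial: 50 × 0.016 = 0.8.
- P(at least one grade 3 patient in 50) = 1 − 0.984^50 = 0.55.

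**Step 5. Chance that a grade 4 patient occurs**

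The article gives no grade 4 GU rate, so the rates p below are assumptions. P(at least one in 50) = 1 − (1 − p)^50.

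| Assumed grade 4 rate | Expected in 50 | P(at least one) |
|---|---|---|
| 0.2% | 0.10 | 0.10 |
| 0.5% | 0.25 | 0.22 |
| 1% | 0.50 | 0.39 |
| 2% | 1.00 | 0.64 |

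The last row lies above the article's own grade 3 rate and is an upper bound for illustration. A patient who also has grade 3 recorded would not be missed, so these are upper figures for a misclassified patient at each rate.

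**Step 6. Effect on the test (two-sided Fisher, 25 vs 25; two-sidedness assumed)**

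- 1 vs 0: P = 1.0. With 0 vs 0 there is nothing to test. At the expected counts the definition does not alter the test result.
- 5 vs 0: P = 0.0502; 6 vs 0: P = 0.0223. Here one grade 4 patient would cross the 5% level, but 5/25 = 20% is 12.5 times the stated 1.6%. At 1.6%, five or more in 25 has probability of about 0.004%.

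The practical effect is on the reported percentages and their direction, much less on significance.

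**The case against.** The best reply is that this is a small feasibility study with a sample size not set by calculation, in which no grade 4 GU event may occur. The events would not be lost either: adverse events go into the case report form, serious related and unexpected ones are reported, the monitoring committee sees accumulating data, and Statistical Analysis plans Fisher tests on adverse event categories without a limit on grade. All of that stands. It shows that the data for a correct endpoint will exist. It does not put grade 4 GU toxicity into any endpoint, and an analysis following the text would leave it out.

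Four stronger readings are tempting, and the article does not support them:

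- *A fatal GU event counts nowhere.* Overall survival is a secondary endpoint, so the death counts there. It is absent only from the GU endpoints.
- *Every grade 4 patient is a primary non-event.* The wording turns on the presence of grade 3, so a patient with grade 3 recorded at any time still counts. This protection may be limited: Table 2, as extracted, shows CTCAE after treatment at 3, 9 and 12 months only, so a grade 3 phase between visits might not be graded.
- *A patient who worsens from grade 2 to 3 leaves the secondary count, making the more toxic arm look better.* That needs a worst-grade rule, which the article does not state. Under the presence wording the patient stays in the secondary count and also enters the primary.
- *The primary comparison is biased.* It would be if a patient with grade 4 or 5 and no grade 3 occurs. No rate is given from which to say how likely that is.

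**Conclusion.** The endpoint is wrong as written. Grade 4 GU toxicity falls in no GU toxicity endpoint, and grade 5 enters only overall survival. This is not detail left to an analysis plan: the grades are stated explicitly, in two places. A plan that followed them would carry the gap forward, and one that analysed grade 3 or higher would depart from the published primary endpoint.

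The size is conditional. Each patient with grade 4 or 5 and no recorded grade 3 moves the comparison by 4 percentage points in favour of the arm with the more severe event. This rests on the literal reading of the grades and on 25 analysed patients per arm. With 0.8 grade 3 events expected in total, one such patient would be a large part of the evidence, but that compares a hypothetical event with an expected count and says nothing about its probability. The sample size is not affected.

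**What to change.** Define the primary endpoint as CTCAE v4 GU toxicity of grade 3 or higher, one yes or no per patient. Keep grades 1 and 2 as the secondary GU endpoint; once the primary starts at grade 3 and is open upwards, the parenthesis does list all the remaining grades. Add a table of the worst GU grade per patient by arm, so that grades 4 and 5 are visible separately. Make the same change in the abstract (Methods) and in Primary and Secondary Endpoints.

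Replacing the secondary endpoint with a cumulative grade 2 or higher, or extending GI toxicity to grade 5, would be a preference and does not follow from this defect.

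The cost is a wording change in two places, carried into the analysis plan if one exists, and one descriptive table. No new data, visits or patients are needed. The change should be made before the data are analysed, so that it cannot appear to depend on the results.
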